### Ecological Momentary Assessment of Cravings, Self-efficacy, and Positive Outcome Expectancies

These predominantly cross-sectional studies, which are subject to recall bias, treat cravings, self-efficacy, and gambling outcome expectancies as stable and enduring traits rather than transient or phasic states [80-82]. However, the reformulated relapse prevention model posits that transient changes in these cognitive processes can constitute phasic responses that interact with tonic processes and determine the likelihood of relapse [15]. Ecological momentary assessment (EMA), an event-level longitudinal methodology, overcomes the limitations of cross-sectional research by repeatedly measuring symptoms, emotions, behavior, and thoughts in real time and in natural environments [80]. Although there is now substantial EMA evidence that momentary cognitive processes (cravings, self-efficacy, and positive outcome expectancies) predict the occurrence of tobacco, alcohol, and substance use [83-89], few EMA studies have explored the associations between these processes and gambling behavior [90-92]. In the available studies, momentary cravings and self-efficacy, but not positive outcome expectancies, have predicted the likelihood of a subsequent gambling episode [90-92]. Moreover, all of these momentary cognitive processes constitute situational determinants of gambling behavior when they interact with other factors implicated in the relapse prevention model, such as high-risk positive reinforcement situations, self-efficacy, coping motives, cravings, positive emotional states, and coping styles [90-92].

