A microrandomized trial (MRT), a form of sequential factorial design in which every participant serves as their own control, will be used to inform the optimization of this JITAI [93,98]. In this MRT, each participant will be randomized to a tailored intervention condition or no intervention control condition at each decision point across a 28-day period [121,122]. The primary aim of the MRT is to explore whether it is worthwhile to deliver a tailored intervention option at a time of cognitive vulnerability. Specifically, the aim is to explore whether, compared with the delivery of no intervention, the delivery of a tailored intervention reduces the probability of a subsequent gambling episode (primary proximal outcome) and improves craving intensity, self-efficacy, and positive outcome expectancies (secondary proximal outcomes). It is hypothesized that the delivery of a tailored intervention will be more effective than no intervention in reducing the probability of a gambling episode and improving craving intensity, self-efficacy, and positive outcome expectancies by the subsequent EMA. Should data allow, secondary exploratory research questions include the following:

*Which type of intervention option is most beneficial at a time of cognitive vulnerability?* Is the delivery of one intervention option (targeting cravings, self-efficacy, or positive outcome expectancies) more likely to reduce the probability of a subsequent gambling episode than the other intervention options?*Under what conditions is the delivery of an intervention option most beneficial?* How do time-variant (EMA) factors (time of day, time of week, craving intensity, self-efficacy, positive outcome expectancies, psychological distress, impulsivity, subjective alcohol intoxication, readiness to change, gambling availability [financial and location], and social context) and time-invariant (preintervention survey) factors (gambling symptom severity, gambling frequency, gambling expenditure, gender, and age) influence the intervention effect on the probability of a subsequent gambling episode?*How do the proximal effects of intervention options change over time as the treatment progresses?* How does the effect of a tailored intervention on the probability of a subsequent gambling episode change over the course of the 28-day MRT?

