### Decision Rules

The decision rules are illustrated in Figure 1. At each decision point during the 28-day MRT, responses to EMA items assessing craving intensity (tailoring variable 1), self-efficacy (tailoring variable 2), and positive outcome expectancies (tailoring variable 3) are used to determine eligibility for the delivery of the tailored intervention, according to a set of predetermined decision rules (scoring >0 on each tailoring variable). At each decision point, participants who do not exceed the cut point for any of the tailoring variables are not eligible for any intervention. These participants will receive a brief encouraging message and their interaction with the app will end. In contrast, participants who exceed the cut point on one or more of the tailoring variables are eligible for a tailored intervention (ie, curbing craving, tackling triggers, *or* exploring expectancies).

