### Microrandomization Protocol

The microrandomization procedure will then be applied, whereby eligible participants will be microrandomized to a tailored intervention condition or no intervention control condition (Figure 1). Overall, the microrandomization procedure will involve eligible participants having a 75% chance of being microrandomized in the tailored intervention condition and a 25% chance of being microrandomized in the no intervention control condition. However, because the reformulated relapse prevention model does not presume that certain factors are more influential than others [15], participants exceeding the cut point on more than one of these tailoring variables will be randomly allocated to a relevant intervention option (curbing cravings, tackling triggers, or exploring expectancies). Specifically, participants who are eligible for 2 intervention options will have a 37.5% chance of receiving either intervention option, and those who are eligible for 3 intervention options will have a 25% chance of receiving any of the intervention options. This microrandomization protocol is fully automated, which guarantees that the administration of treatments and assessment of outcomes are blinded.

Following completion of each EMA, participants who are microrandomized to the no intervention control condition will be sent an encouraging message, and their interaction with the app will end. Participants microrandomized to the tailored intervention condition will be sent to the relevant intervention dashboard, which comprises a menu of intervention activities from which they can select. Specifically, participants who are allocated to the craving intervention will be taken to the craving intervention dashboard and asked to select an intervention activity. In contrast, participants who are allocated to the self-efficacy and expectancies interventions will be asked to select a specific type of trigger or expectation, administered an EMA item specific to their selected trigger or expectation (Multimedia Appendix 3), then taken to the relevant intervention dashboard, and asked to select an intervention activity.

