### Statistical Analyses

To assess the research questions, the method of generalized estimating equations (GEE) will be used, with an appropriate link function for the outcome of interest (eg, identity and logit). Although the intention is to use an exchangeable working correlational structure for analyses, alternative correlational structures based on the observed within-person correlation pattern over the course of the study (eg, independent or autoregressive) will be considered. For all MRT analyses, the (lagged) outcome of interest (eg, gambling episode at Time_t+1_) will be regressed on to a variable denoting the intervention received (eg, intervention options 1, 2, and 3 or no intervention) at Time_t_, as well as covariates (including unbalanced time, time since prior assessment, and other forms of help-seeking). To assess the primary research question and secondary research question 1, the analyses will examine the effects of the tailored intervention versus no intervention control on the probability of a subsequent gambling episode, stratified analyses focusing on each intervention option separately versus no intervention control (on the specific outcome related to each intervention option; ie, craving intensity, self-efficacy, and positive outcome expectancies), and formal tests comparing the magnitude of each intervention with the no intervention condition on the probability of a subsequent gambling episode. Secondary research questions 2 and 3 will be examined by specifying the interaction terms between the intervention variable and the interaction variable of interest (eg, psychological distress and time). Consideration will be given to making appropriate adjustments in line with modern causal methods for assessing effect moderation [154].

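### The option-specific contrasts set each intervention option against a single control category without accounting for which flags were raised or the unequal assignment probabilities, so they can be biased when no option has any effect

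*Protocol article*

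**What the plan says.** **Eligibility (Decision Rules).** The cut point is a score above 0 on a tailoring variable, and "participants who exceed the cut point on one or more of the tailoring variables are eligible for a tailored intervention".

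**Assignment (Microrandomization Protocol).** The section describes "eligible participants having a 75% chance of being microrandomized in the tailored intervention condition"; the other 25% go to control. With several flags, "participants exceeding the cut point on more than one of these tailoring variables will be randomly allocated to a relevant intervention option". For two flags the section states that "participants who are eligible for 2 intervention options will have a 37.5% chance of receiving either intervention option". With three flags, each option has probability 25%.

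**Analysis (Statistical Analyses).** For all analyses of the microrandomized trial, the next outcome is regressed on the intervention received. The example coding has four levels: the three options and one no-intervention level. The named covariates are time, time since the prior assessment and other help-seeking. Each option is then compared with control on its own target outcome, in "stratified analyses focusing on each intervention option separately versus no intervention control", and again on gambling. The section does not say which control points enter each comparison. It names no weighting and no covariate for flags, tailoring scores or assignment probability.

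**Question (Research Questions).** Secondary question 1 asks whether one option is "more likely to reduce the probability of a subsequent gambling episode than the other intervention options".

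**The concern.** Only the choice between any tailored option and control is made with constant probability at every eligible point. Which option is given depends on which flags were raised and how many. Every recipient of the craving option had a craving flag, whereas a single control category also contains points with no craving flag. If flags predict the outcome, the two groups differ before any treatment acts.

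The protocol says that they do, at least in part. Its review of earlier momentary-assessment studies reports that "momentary cravings and self-efficacy, but not positive outcome expectancies, have predicted the likelihood of a subsequent gambling episode". The states that trigger the three options therefore need not carry the same risk of gambling.

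Two sets of results are exposed. The craving, self-efficacy and expectancy outcomes are hypothesised secondary proximal outcomes, and the analysis section specifies them through these contrasts. Secondary question 1 is also answered this way, although it asks how options compare with each other and the stated tests compare each with control.

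**Working it through.** **1. The plan's own figure.** The article gives no figure for the option contrasts. Its power statement concerns the tailored-intervention effect on gambling. With its inputs as printed (120 participants, availability 0.3, randomization probability 0.25, outcome risk 0.25 without intervention, relative risk 1.21, alpha .05 taken as two-sided) and 3 × 28 = 84 decision points:

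- Available points: 120 × 84 × 0.3 = 3,024.
- Risks: 0.25 and 0.25 × 1.21 = 0.3025.
- Var(log RR) = [0.6975/(0.25 × 0.3025) + 0.75/(0.75 × 0.25)]/3,024, so SE = 0.0661.
- z = ln(1.21)/0.0661 = 2.88; power = Φ(2.88 − 1.96) = 82%.

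This agrees with the stated power above 80%. The planned effect of 1.21 serves below only as a yardstick.

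**2. Null calculation for gambling.** Assumptions, none of them in the article: next-window gambling risk .12, plus .14 if craving is flagged, plus .08 if self-efficacy is flagged, plus 0 for expectancies; independent flags of equal prevalence; no option has any effect. From the article: with m flags, each relevant option has probability 0.75/m and control 0.25.

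At 50% prevalence the seven eligible flag patterns are equally likely (C, S, E = craving, self-efficacy, expectancy):

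| Pattern | Risk | m |
|---|---|---|
| C | .26 | 1 |
| S | .20 | 1 |
| E | .12 | 1 |
| C+S | .34 | 2 |
| C+E | .26 | 2 |
| S+E | .20 | 2 |
| C+S+E | .34 | 3 |

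- All controls: (.26 + .20 + .12 + .34 + .26 + .20 + .34)/7 = 1.72/7 = .2457.
- Recipients of an option are spread over its four patterns in proportion to 1/m, that is 1, 1/2, 1/2 and 1/3, which sum to 2.333.
- Craving option: (.26 + .34/2 + .26/2 + .34/3)/2.333 = .2886. RR = .2886/.2457 = 1.17.
- Self-efficacy option: (.20 + .34/2 + .20/2 + .34/3)/2.333 = .2500. RR = 1.02.
- Expectancy option: (.12 + .26/2 + .20/2 + .34/3)/2.333 = .1986. RR = 0.81.

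The same calculation at other prevalences:

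| Each flag raised | Craving option vs all controls | Expectancy option vs all controls |
|---|---|---|
| 30% | 1.25 | 0.73 |
| 50% | 1.17 | 0.81 |
| 80% | 1.07 | 0.93 |
| 95% | 1.02 | 0.98 |

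If an expectancy flag also adds .08, the 50% row becomes 1.09 and 0.96. With equal risk increments and equal prevalence, every relative risk is exactly 1.00.

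**3. Restricting controls to points flagged for the option (50% row).** Control risks become .30, .27 and .23. The null relative risks are .2886/.30 = 0.96, .2500/.27 = 0.93 and .1986/.23 = 0.86. Bias remains because points with several flags are under-represented among recipients of any one option, while controls are drawn at 25% whatever the pattern.

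**4. Restricting and weighting.** Weighting option points by m/0.75 and control points by 1/0.25 gives both groups the same flag-pattern mix. All three relative risks are then 1.00.

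**5. False-positive rates.** In 300 simulated null trials (200 participants, about 5,400 eligible points, 50% flag rates, flag odds ratios 2, 1.5 and 1, logit GEE, exchangeable), results in the order craving, self-efficacy, expectancy were:

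| Analysis | Odds ratios | Rejections at 5% |
|---|---|---|
| Four-level variable | 1.22, 1.01, 0.77 | 60%, 5%, 76% |
| Restricted and weighted | 0.99, 1.00, 1.00 | 5.7%, 4.0%, 7.3% |
| Pooled tailored vs control | 0.99 | 4.3% |

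**6. Next craving score.** At 50% prevalence 3/7 = 43% of all controls have no craving flag. Assuming a mean score of 2 when flagged and a carry-over to the next assessment of 0.2 to 0.5, the false difference against the craving option is 0.43 × 2 × 0.2 = 0.17 to 0.43 × 2 × 0.5 = 0.43 points. At 95% prevalence (5% of controls unflagged) it is 0.02 to 0.05.

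**The case against.** The strongest reply is that pooling of controls is inferred. The article does not say that all eligible controls enter each comparison. The word stratified may mean restriction to points eligible for the option, the four-level coding is given as an example, and the covariate list is open-ended. An article condenses, and an analysis plan may add detail. This is a fair doubt about intent. It does not dispose of the point, because restriction alone still gives null relative risks of 0.96, 0.93 and 0.86 in the 50% case, and the adjustment that the design requires is not named. The closing remark on modern causal methods promises only consideration, and concerns effect moderation.

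The second reply is about size, and it stands. The cut point is the lowest possible, so several flags may often be raised together, and the bias is then small. The same review of earlier studies adds that all three processes, expectancies included, matter in interaction with other factors, so a zero expectancy effect is an assumption.

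A reader might go further and infer that the craving option will look harmful and the expectancy option helpful. The article gives no flag prevalence, correlation or flag-specific risk, so neither the direction nor the size can be asserted. A reader might also infer that these contrasts decide which options are dropped. The Discussion names dropping less effective options only as something that optimization may involve, and secondary question 1 is exploratory and conditional on the data.

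**Conclusion.** The point holds for the option-specific contrasts. Followed as written, they compare groups that differ in flag pattern by design, and they are biased under no effect whenever flag pattern predicts the outcome and the patterns do not happen to balance. Under the assumed risks, the null relative risks for the craving and expectancy options run from about 1.25 and 0.73 to about 1.02 and 0.98 as flag prevalence rises from 30% to 95%. At the low end, the bias is as large as the planned effect of 1.21. The gambling bias against all controls is zero with equal flag risks and equal prevalence, or if flags do not predict gambling.

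It would be wrong to read this as a flaw in the primary result. The pooled tailored-versus-control contrast on gambling is randomized 75:25 at every eligible point and is unaffected. For that reason, and because secondary question 1 is exploratory, this should be fixed but does not undermine the trial. Confidence is high in the mechanism, moderate in what the plan intends, and low in the size.

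**What to change.** State the following in the analysis plan before the data are analysed:

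- For option k, analyse only decision points where tailoring variable k exceeded the cut point.
- Within those points, weight by the inverse of the known assignment probability: 1/0.75, 1/0.375 or 1/0.25 for option points with one, two or three flags, and 1/0.25 for control points. Stratifying by, or adjusting for, the full flag pattern is an acceptable alternative.
- For secondary question 1, add direct option-versus-option contrasts at points where both options were eligible. There the options were randomized against each other with equal probability.
- Report the frequency of each flag pattern, so that readers can judge how much the choice of control points matters.

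The cost is a few sentences and a few lines of code. The flags come from each momentary assessment and the probabilities are fixed by design, so trial conduct does not change. The downside is fewer control points and some loss of precision in each option contrast.

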Two other gambling JITAIs that use active assessments via smartphone-delivered EMAs to collect data on internal states have been developed: *Jeu-contrôle* [114] and *GamblingLess: Curb Your Urge* [115,116]. Yet to be evaluated, *Jeu-contrôle* is a publicly available JITAI that uses EMAs to provide personalized feedback in relation to goal limits, with a view to supporting adherence to expenditure and time limits. In contrast, *GamblingLess: Curb Your Urge* is informed by the relapse prevention model and aims to reduce gambling cravings to prevent subsequent gambling episodes. This intervention, which was adapted from *GamblingLess*, an evidence-based web-based self-directed gambling program [41,43,115-120], tailors craving management activities to EMAs evaluating craving intensity and also provides these activities on demand. Key stakeholders rated the intervention content, helpfulness, acceptability, and usability highly and indicated that they would recommend the app to gamblers given its potential to increase gambling knowledge, attitudes, awareness, behavior change, intention to change, and help-seeking [115,116]. A pilot study of this JITAI [116] revealed promising findings, with more than a 70% reduction in the average number of gambling episodes and craving occurrences during the intervention period and a 10% decrease in momentary craving intensity immediately after a recommended intervention. There were also significant medium-to-large reductions in gambling symptom severity, gambling frequency, gambling expenditure, cravings, and self-efficacy at the postintervention and 1-month follow-up evaluations. At the 1-month follow-up evaluation, nearly half of the participants (10/21, 48%) reported recovery or improvement in the severity of gambling symptoms.

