### Within-Group Follow-up Evaluation

A within-group evaluation of outcomes over a 6-month follow-up period will supplement the MRT to (1) evaluate within-group change over a longer period and (2) explore predictors of longer-term treatment outcomes (including app use over the 6-month follow-up period). Although the preintervention survey will be automated via the app before beginning the 28-day MRT period, participants will be prompted by email to complete the postintervention and follow-up surveys via Qualtrics (Qualtrics XM). Descriptive and covariate measures will include participant type (gambler, family member or friend, and clinician, researcher, or policy maker), sociodemographic characteristics, problem gambling activities, intended gambling behavior (measured using the Timeline Follow-Forward, a novel adaptation of the Timeline Follow-Back [148]), and other help-seeking (measured using the Help Seeking Questionnaire [149]). The primary outcome will be gambling symptom severity (measured using the Gambling Symptom Assessment Scale [129]), and secondary outcomes will include gambling frequency and expenditure (measured using a timeline follow-back at the preintervention evaluation, the EMA event record data at the posttreatment evaluation, and single items at the 6-month evaluation) and the cognitive processes targeted by the intervention: craving severity (measured using the Penn Gambling Craving Scale [25]), self-efficacy (measured using the Brief Situational Confidence Questionnaire-Gambling [130]), and positive outcome expectancies (measured using the Excitement, Escape, and Money subscales of the Gambling Outcome Expectancies Scale [69]; Multimedia Appendix 4). Each evaluation will be completed in approximately 10 to 15 minutes. Ideally, follow-up evaluation surveys will also be conducted 12 and 24 months after the intervention, but this will be dependent on obtaining additional funding.

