To explore the long-term outcomes of the intervention (within-group follow-up evaluation), distal outcomes will be assessed using GEE by regressing the outcome of interest (eg, gambling symptom severity) on a variable denoting time (ie, preintervention, postintervention, 6-month follow-up variables) and covariates. The factors associated with longer-term treatment outcomes will also be explored using GEE by regressing the outcome of interest (eg, clinically significant change in gambling symptom severity) with selected preintervention, postintervention, and app use variables (eg, the number of participant-initiated EMAs completed in the 6-month follow-up period). Where appropriate, missingness will be addressed using multiple imputation, with appropriate accounting for the multilevel nature of the data (eg, see multilevel multiple imputation [155]).

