### Clinical Significance

Supplementary analyses will consider the clinical significance of any effect (ie, meaningful changes in the participant’s life) [156]. Effect sizes will be calculated for all primary and secondary outcomes. These group-level examinations of effectiveness will also be supplemented by metrics of individual-level change for all primary and secondary outcomes. A reliable change index will be used to assess changes beyond those attributable to chance or measurement error [157]. Clinically significant change, as outlined by Jacobson and Truax [156], will subsequently be calculated using functional score ranges where possible (Gambling Symptom Assessment Scale score of ≤20) or a convention of at least a 25% change in scores in the positive direction [158]. At the posttreatment and 6-month follow-up evaluations, each participant’s status will be defined as *recovered* (final score falls into the functional range and corresponds to a reliable change), *improved* (final score falls into the dysfunctional range and corresponds to a reliable change), *unchanged* (final score does not correspond to a reliable change), or *deteriorated* (final score corresponds to a relative change in the negative direction).

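### For the exploratory predictors of longer-term outcome, the only outcome named is a cut-point status rather than the symptom score; used as a yes/no outcome, it loses power that the score would keep

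*Protocol article*

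**What the plan says.** The Within-Group Follow-up Evaluation section gives the follow-up two aims: to evaluate change over a longer period and to explore predictors of longer-term outcome. On outcomes it says "The primary outcome will be gambling symptom severity (measured using the Gambling Symptom Assessment Scale [129"]).

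The Statistical Analyses section then treats the two aims differently.

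- For change over time: "distal outcomes will be assessed using GEE by regressing the outcome of interest (eg, gambling symptom severity) on a variable denoting time".
- For predictors, the purpose is exploratory: "The factors associated with longer-term treatment outcomes will also be explored using GEE". The model for this second aim is described as "regressing the outcome of interest (eg, clinically significant change in gambling symptom severity) with selected preintervention, postintervention, and app use variables".

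The same section sets up GEE in general terms, "with an appropriate link function for the outcome of interest (eg, identity and logit").

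The Clinical Significance section opens with "Supplementary analyses will consider the clinical significance of any effect". It defines the status from a reliable change index and "functional score ranges where possible (Gambling Symptom Assessment Scale score of ≤20"), with a 25% change convention where no functional range exists. Each participant is then placed in one of four levels: recovered, improved, unchanged or deteriorated.

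**The concern.** Two neighbouring sentences move from the score to a status derived from it, and the analysis text gives no reason for the move. The status contains no outcome information beyond the scores already collected at each wave. Everyone on the same side of a cut is treated alike, however far they moved.

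Entry is open to people at any level of symptom severity (Participant Recruitment and Reimbursement). Someone who enters with a low score has little room for a reliable improvement and will tend to be classed as unchanged, whatever the predictor does. A baseline-adjusted score still uses that person's data.

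At stake is the second aim of the follow-up. In a sample of about 120, a modest predictor, app use included, could be missed mainly because of how the outcome was coded.

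**Working it through.** **Plan's own figure.** The article states no power for the predictor analysis. The figure of more than 80% power at 120 participants in the Sample Size section belongs to the microrandomized comparison of gambling episodes. What carries over is the retained number: 200 × (1 − 0.40) = 120. Applying that attrition rate to the follow-up surveys is itself an assumption.

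**Inputs from the article**
- Retained sample 120. With the pilot's 19% attrition it would be 200 × 0.81 = 162.
- Responder share 10/21 = 48%, from the pilot at 1 month: "nearly half of the participants (10/21, 48%) reported recovery or improvement in the severity of gambling symptoms".

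**Assumed inputs**
- One standardised predictor with partial correlation r from 0.10 to 0.40.
- Correlation of 0.5 between preintervention and follow-up score.
- Two-sided 5% test and one follow-up wave.
- A 30% responder share as an alternative.

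**Check 1: formula, simple correlation.** Splitting a normal outcome at prevalence q multiplies r by φ(z)/√(q(1−q)), where z is the normal quantile at q. For q = 0.48 this is 0.3984/√(0.48 × 0.52) = 0.7975. Squared, it is 0.636, so about 64% of the information is kept. Power comes from the noncentral t distribution with noncentrality r√n/√(1−r²).

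At n = 120 and r = 0.25:
- Score: 0.25 × 10.954/0.968 = 2.83, power 80.1%.
- Split: r = 0.25 × 0.7975 = 0.199; 0.199 × 10.954/0.980 = 2.23, power 59.9%.
- Loss: 20.2 points.

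By the same formula the loss is 5.4 points at r = 0.10, 18.3 at 0.20, 16.4 at 0.30 and 4.2 at 0.40.

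**Check 2: simulation with baseline adjustment.** This is closer to the defined status, which rests on change from baseline. The model is Y6 = 0.5·Y0 − √0.75·(r·X + √(1−r²)·e), with X, Y0 and e standard normal. The change Y0 − Y6 has variance 1 + 1 − 2 × 0.5 = 1. A responder is anyone whose change exceeds the cut giving the stated prevalence. Linear regression of Y6 on X and Y0 is compared with logistic regression of responder on X and Y0, with 4,000 runs per cell.

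| n = 120, 48% responders | Score | Met / not met | Loss (points) |
|---|---|---|---|
| r = 0.10 | 18.5% | 12.5% | 6 |
| r = 0.20 | 58.9% | 36.7% | 22 |
| r = 0.25 | 78.3% | 52.7% | 26 |
| r = 0.30 | 91.8% | 70.7% | 21 |
| r = 0.40 | 99.6% | 92.3% | 7 |

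Other runs of this model gave losses of 22 to 26 points for r of 0.20 to 0.30. A variant that also required a functional-range score gave much the same.

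**Sensitivity**
- 30% responders, n = 120: losses of 27, 31 and 27 points at r = 0.20, 0.25 and 0.30.
- n = 162, 48% responders: 23, 24 and 14 points.
- n = 200, 48% responders: 24, 19 and 9 points.
- Four ordered levels kept, n = 120: about 12 to 17 points for r of 0.20 to 0.30 with baseline adjustment, and about 8 points at r = 0.25 with a simple correlation.

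**The case against.** The strongest reply is that the sentence gives an example. It does not say that the status replaces the score, and the general GEE text already allows an identity link. A reader might infer that the score is ruled out for the predictor models. The article does not support that, so the point is limited to which outcome is named.

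A reader might also infer that the status will be collapsed to two levels. The article defines four and states no collapse, so the larger losses are conditional on a met/not-met coding. That coding is plausible, because clinically significant change is usually reported that way and the only links mentioned are identity and logit. It is still an inference.

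Three further limits stand. The analysis is exploratory and carries no power claim. A loss of 20 points or more is not a general result: it depends on the assumed effect size and prevalence, and it shrinks for very weak or strong predictors. The 48% comes from 21 people at 1 month, not from a 6-month evaluation.

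The Discussion does value clinical impact alongside statistical significance, and who reaches a clinically significant change is a fair question in its own right. That justifies keeping the status model. It does not justify making it the only outcome named. A journal article may leave a full list of exploratory outcomes to the analysis plan, but the example it chose to print is the less informative one.

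**Conclusion.** The point holds as a modest improvement to an exploratory analysis. The one outcome named for the predictor aim is a status derived from the primary follow-up score, and the article elsewhere calls that kind of analysis supplementary.

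If the status is coded as met or not met, the cost is roughly 20 to 25 power points for partial correlations of 0.20 to 0.30, and about 6 to 8 points at 0.10 or 0.40. This assumes 120 retained, a baseline correlation of 0.5 and about 48% responders. A rarer status costs more; ordered levels cost less.

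The analysis of change in symptom severity over time is not affected. Nor does the point extend to the secondary outcomes, for which the article names no cut-point predictor model.

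**What to change.** In the Statistical Analyses section, name the continuous Gambling Symptom Assessment Scale score at postintervention and 6 months, adjusted for the preintervention score, as the main outcome of the predictor models (GEE, identity link). Predictors recorded at or after postintervention, such as app use during follow-up, should be related only to the 6-month score. Keep clinically significant change as a supplementary model, and state whether it uses two levels or all four in order.

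The cost is a change of wording, with no new data or participants. The small downside is that the main coefficients are in scale points rather than odds of recovery; the supplementary model still supplies the latter.
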